#### Analysis plan, aim 4 (Frailty)

Our primary exposure for Aim 4 is ‘frailty’ operationalized using the VA-FI. We will model the VA-FI as a 3-level categorical measure (i.e., non-frail, pre-frail, frail). Using a similar modeling strategy as for Aims 1–3, we will use an ordinal logistic mixed modeling strategy to estimate the association of clinic-collected functional status measures on frailty (VA-FI; sensitivity analyses with other measures [69]). Inference will be based on estimated odds ratios associated with functional status measures, with associated 95% CIs and/or *p*-values.

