### Study goals and objectives

The goals of the PACT Functional Status Screening Initiative are four-fold: (1) measure clinician- and organization-level implementation outcomes; (2) compare the effectiveness of a standard versus enhanced implementation approach to improve adoption; (3) measure patient-level clinical effectiveness of the intervention; and (4) test the effectiveness of electronic health record (EHR)-based frailty screening for identifying veterans at risk for functional impairment.

We will evaluate this initiative by conducting a hybrid type II implementation-effectiveness cluster-randomized adaptive trial [32–34]. During implementation, we will identify sites with low uptake and compare a standard bundle of implementation strategies to an enhanced bundle [35]. Based on our preliminary work [31], we hypothesize that this will lead to increased identification and improved management of functional impairment while providing data to inform VA strategic planning related to long-term services and supports and implementation of new programs. Specifically, we will generate data to guide VA’s investment in non-institutional care programs (including home- and community-based services) that can enhance veterans’ ability age in place. The findings will also allow for targeting and testing of novel programs to address impairments and prevent or delay further functional decline and associated acute care utilization.

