#### Aim 4 (Frailty)

Frailty will be measured using the validated VA Frailty Index (VA-FI), calculated using the cumulative deficit method [67]. The VA-FI includes up to 31 age-related health deficits based on VA EHR diagnostic and procedure codes [46, 68]. Categories include non-frail (0–0.1), pre-frail (0.11–0.2), and frail (> 0.2). Functional status will be measured from Health Factors. In sensitivity analyses, we will examine other EHR frailty indices (e.g., JEN Index [69]).

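### Aim 4 uses the VA Frailty Index only as three groups, which costs precision and limits what the analysis can say about identifying impairment; the full-scale score should be the primary form

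*Protocol article*

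**What the plan says.** The fourth study goal is to "test the effectiveness of electronic health record (EHR)-based frailty screening for identifying veterans at risk for functional impairment" (Study goals and objectives).

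The outcome section for Aim 4 describes the index and its cuts: "The VA-FI includes up to 31 age-related health deficits based on VA EHR diagnostic and procedure codes", and "Categories include non-frail (0–0.1), pre-frail (0.11–0.2), and frail (> 0.2").

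The analysis plan for Aim 4 fixes how the index enters the main model: "We will model the VA-FI as a 3-level categorical measure (i.e., non-frail, pre-frail, frail"). It names the index's role, "Our primary exposure for Aim 4 is ‘frailty’ operationalized using the VA-FI", and then the model: "we will use an ordinal logistic mixed modeling strategy to estimate the association of clinic-collected functional status measures on frailty". The reported quantity follows: "Inference will be based on estimated odds ratios associated with functional status measures".

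The sensitivity analyses named for Aim 4 substitute other EHR frailty indices, with the JEN index as the example. They do not change the scale on which the VA-FI is used.

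**The concern.** The VA-FI is computed as a near-continuous score and then cut. With all 31 deficits available, the three groups are 0–3, 4–6 and 7–31 deficits, so everyone from 7 deficits upward is treated alike. If the index works as intended, that is where impairment should be most common.

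The fourth goal is about finding veterans at risk. Three groups can evaluate only two preset thresholds. They cannot show whether another threshold would do better, or how risk changes within the frail group. They also give a less precise estimate from the same patients, with no saving, because the full score has to be calculated before it is cut.

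**Working it through.** The protocol gives no power, precision or information figure for Aim 4, so there is nothing of its own to reproduce.

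**Inputs from the protocol**
- Up to 31 deficits; cuts at 0.1 and 0.2 (Aim 4, Frailty).
- More than 5,000 veterans expected from 8 sites; design effect 4.4 for Aim 3 (Missing data and power analysis).
- Impairment prevalence 459,000 / 2,800,000 = 16.4% (Background). This is for enrolled veterans aged 65 and older, whereas the initiative covers ages 60 and older, so it is a proxy.

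**Assumptions (not in the protocol)**
- Deficits are beta-binomial out of 31, with five mean/SD pairs from 0.12/0.08 to 0.30/0.12.
- For the predictor calculations, the log-odds of impairment are linear in the index.
- Site clustering is ignored unless stated.

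**Step 1: what the groups contain.** 3/31 = 0.097, 4/31 = 0.129, 6/31 = 0.194 and 7/31 = 0.226. The groups are 0–3, 4–6 and 7–31 deficits.

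**Step 2: loss in the planned model (index as ordinal response).** For a small effect under proportional odds, the efficiency of three levels relative to the full grid is

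RE = (1 − Σp_c³) / (1 − Σp_k³),

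where p_c are the three group shares and p_k the shares of the 32 possible scores. Example at mean 0.20, SD 0.10: the shares are 0.201, 0.375 and 0.425, so 1 − Σp_c³ = 0.863. The full grid gives 0.990, and 0.863 / 0.990 = 0.87.

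**Step 3: loss if the three levels are used as a predictor.** Information kept is the between-group variance of the index divided by its total variance.

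**Step 4: discrimination.** AUC of the full and three-level index, at an assumed odds ratio of 2.0 per SD and 16.4% prevalence.

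| Mean / SD | RE, ordinal response | Interval width, 1/√RE | Information kept as predictor | AUC full → 3 levels |
|---|---|---|---|---|
| 0.12 / 0.08 | 0.83 | 1.10 | 0.83 | 0.69 → 0.67 |
| 0.16 / 0.09 | 0.89 | 1.06 | 0.82 | 0.69 → 0.67 |
| 0.20 / 0.10 | 0.87 | 1.07 | 0.76 | 0.69 → 0.65 |
| 0.25 / 0.12 | 0.77 | 1.14 | 0.65 | 0.69 → 0.62 |
| 0.30 / 0.12 | 0.56 | 1.34 | 0.51 | 0.69 → 0.59 |

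The loss is therefore 11–44% for the planned ordinal model and 17–49% as a predictor. A separate calculation with a beta-shaped score rounded to the 31-item grid (mean 0.10–0.30, SD 0.07–0.13) gave ordinal-model losses of 11–32% at means up to 0.20, 21–36% at 0.25 and 40–74% at 0.30. The size depends on how concentrated patients are in one group.

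**Step 5: spread of risk within the frail group.** At mean 0.20 and an odds ratio of 2.0 per SD, predicted impairment is 17% at 7 deficits and 49% at 14. Both are labelled frail.

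**Step 6: is the planned odds ratio biased?** Simulation with 5,000 patients, 16% impaired, true log odds ratio 0.90 and 20 runs for each of four sets of cuts. Mean estimates with 3 versus 15 levels were 0.91 vs 0.91, 0.87 vs 0.89, 0.93 vs 0.93 and 0.89 vs 0.89. Grouping does not shift the estimate; it enlarges the standard error.

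**Step 7: is detection at risk?** With the full score as predictor, the odds ratio per SD detectable with 80% power is exp(2.80 / √(5,000 × 0.164 × 0.836)) = exp(2.80 / 26.2) = 1.11. In the worst row (information kept 0.51) it becomes exp(0.107 / √0.51) = 1.16. If the Aim 3 design effect of 4.4 were also applied, which the protocol does not say for Aim 4, the two values are exp(0.107 × √4.4) = 1.25 and exp(0.107 × √4.4 / √0.51) = 1.37. A moderate association remains detectable throughout.

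**The case against.** Several points on the other side stand.

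- The cuts are fixed in advance on an index the protocol calls validated, with sources cited. They are not data-driven, and threshold groups are a natural format for screening. That makes the groups a reasonable display; it does not make them the best primary scale for judging how well the index identifies impairment.
- A reader might infer that grouping makes the plan understate how well frailty identifies impairment. The planned model does not support that. With frailty group as the response, merging levels leaves the odds ratio unchanged under proportional odds, as step 6 shows. Discrimination falls only when the three-level score is used as a predictor, and the plan names no AUC. The predictor reading is not invented, however: the plan calls frailty the primary exposure, and the fourth goal runs from frailty to impairment.
- The large losses need most patients to fall in one group. In four of the five assumed distributions the loss in the planned model is 11–23%.
- With this sample size, no yes/no conclusion about an association is shown to change.
- A condensed article may leave additional sensitivity analyses to a fuller document. For that reason the point is not that a continuous sensitivity analysis is absent. It is that the stated primary form is the three-level one.

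**Conclusion.** The point holds as a matter of precision and fitness for purpose; it does not invalidate the plan. Using three levels as the only stated form of the VA-FI loses about 11–44% of efficiency in the planned ordinal model (intervals about 6–34% wider), or about 17–49% of information if the levels serve as a predictor. Both ranges rest on assumed distributions (mean 0.12–0.30, SD 0.08–0.12). They should not be read as properties of the trial, because the protocol gives no VA-FI distribution. The AUC and within-group risk figures rest further on an assumed odds ratio of 2.0 per SD, linear log-odds and a proxy prevalence.

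The planned odds ratio is not biased under proportional odds, and detection of a moderate association is not in doubt. What is lost is precision and, for the stated goal of identifying at-risk veterans, discrimination and the shape of the risk relation. Odds ratios for functional status across three preset frailty groups do not supply these.

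**What to change.** In the Aim 4 analysis plan:

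- Make the full-scale VA-FI, per 0.1 or as a restricted cubic spline to allow non-linearity, the primary form in a mixed model relating it to functional impairment.
- Report the AUC and predicted impairment risk across the range of the index.
- Keep non-frail, pre-frail and frail as a secondary display, with sensitivity and specificity at 0.1 and 0.2.
- Treat the JEN and any other frailty index in the same way, so that the indices are compared on their full scales.

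Putting impairment on the left of the model also makes it agree with the description of frailty as the exposure.

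The cost is a change of wording and a little more analysis. No new data are needed, because the score is computed before it is cut. The result is slightly harder to explain than three labels, which remain available as the secondary display.

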**Fig. 2 Fig2:**
[figure not shown]
Flow Diagram for Adaptive Cluster-Randomized Controlled Trial. The figure shows the sequence of the four implementation periods, randomization, and cross-over allocation

In keeping with our operational partners’ interest in developing proactive approaches to identify high-risk veterans and intervene to prevent or delay functional impairment and associated acute care utilization, we will test the association of clinic-collected functional status measures with automated EHR-based frailty measures. Because frailty typically develops before functional impairment and may be a promising target for intervention [44–47], these findings will clarify how the two approaches might complement and inform one another.

Based on Primary Care and Office of Nursing Services capacity and input, we will implement the intervention in two waves, with 8 sites total. Sites may range in size depending on organizational capacity (e.g., a full community-based clinic or several primary care teams within a larger site). For both waves, we will cluster at the site level. Each site will move through three phases: Pre-Implementation, Implementation, and Sustainment (Fig. 3) [48].

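### Aim 4 calls frailty the exposure but describes a model in which frailty is the response, the reverse of the stated goal; the roles need to be reconciled

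*Protocol article*

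**What the plan says.** All references are to the protocol article.

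- **Study goals and objectives**, goal 4: "test the effectiveness of electronic health record (EHR)-based frailty screening for identifying veterans at risk for functional impairment". The index is the screen; impairment is the target.
- **Overview of study design** (text after Fig. 2) gives the presumed time order: "Because frailty typically develops before functional impairment and may be a promising target for intervention". The same paragraph describes the planned test only as an association between the two kinds of measure. The Aim 4 row of Table 3 is equally neutral.
- **Analysis plan, aim 4 (Frailty)** assigns the roles. First: "Our primary exposure for Aim 4 is ‘frailty’ operationalized using the VA-FI". Next, the scale: "We will model the VA-FI as a 3-level categorical measure". Then the model: "we will use an ordinal logistic mixed modeling strategy to estimate the association of clinic-collected functional status measures on frailty". Finally the estimand: "Inference will be based on estimated odds ratios associated with functional status measures".

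No other section specifies a model for Aim 4.

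**The concern.** An odds ratio belongs to a regressor. If inference rests on odds ratios for functional status, then functional status is the predictor. The only ordered variable that the paragraph defines is the three-level VA-FI, so the VA-FI becomes the ordinal response. The variable named as the exposure is then the outcome of the model.

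Goal 4 needs the opposite: how the odds or probability of impairment differ between pre-frail, frail and non-frail veterans. With two binary variables the unadjusted odds ratio is the same in either direction. With a three-level ordinal response it is not. The usual proportional-odds model returns one ratio per functional measure, comparing impaired with unimpaired veterans on the odds of being in a higher frailty category. That quantity does not answer goal 4.

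**Working it through.** The article gives no effect size, sample size or power for Aim 4, so there is no stated figure to reproduce. The check has two parts.

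**1. Roles of the variables**

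| Source | Frailty (VA-FI) | Functional status |
|---|---|---|
| Goal 4 | screen | condition to be found |
| Overview of study design, time order | earlier | later |
| Overview of study design, planned test; Table 3 | associated | associated |
| Aim 4 analysis, first sentence | exposure | (outcome, by implication) |
| Aim 4 analysis, model and inference sentences | response | predictor |

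The last row contradicts the row above it and reverses the first two. The neutral wording in the third row is compatible with either direction and does not settle the matter.

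**2. Does the direction matter?**

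Inputs:
- Frailty mix of 40/30/30% (non-frail/pre-frail/frail): assumed.
- Impairment risk by category: assumed. Pattern A is 10/11/30%; pattern B is 5/20/24%.
- Overall impairment: 0.40×10% + 0.30×11% + 0.30×30% = 16.3% in A, and 0.40×5% + 0.30×20% + 0.30×24% = 15.2% in B. The Background section gives 459,000 of 2.8 million = 16.4%, for ages 65 and over; the trial includes ages 60 and over.
- Binary impairment, no site clustering, one time point.

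*Direction implied by goal 4.* OR = [p_k/(1−p_k)] / [p_0/(1−p_0)], where p_0 is the risk in non-frail veterans.
- A: pre-frail (0.11/0.89)/(0.10/0.90) = 1.11; frail (0.30/0.70)/(0.10/0.90) = 3.86.
- B: pre-frail (0.20/0.80)/(0.05/0.95) = 4.75; frail (0.24/0.76)/(0.05/0.95) = 6.00.

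*Direction as written.* The population shares in the three frailty categories are:
- A: impaired 0.040/0.033/0.090; unimpaired 0.360/0.267/0.210.
- B: impaired 0.020/0.060/0.072; unimpaired 0.380/0.240/0.228.

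The cumulative odds ratios at the two cut-points are:
- A: pre-frail or worse (0.123/0.040)/(0.477/0.360) = 2.32; frail (0.090/0.073)/(0.210/0.627) = 3.68.
- B: pre-frail or worse (0.132/0.020)/(0.468/0.380) = 5.36; frail (0.072/0.080)/(0.228/0.620) = 2.45.

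A proportional-odds model fitted by maximum likelihood pools each pair into one ratio:

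| Frailty mix | As written, A | As written, B | Odds ratios for impairment, A | Odds ratios for impairment, B |
|---|---|---|---|---|
| 40/30/30 | 3.14 | 3.09 | 1.11, 3.86 | 4.75, 6.00 |
| 25/30/45 | 3.42 | 2.45 | unchanged | unchanged |
| 50/30/20 | 2.75 | 3.53 | unchanged | unchanged |

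At 40/30/30 the model as written reports nearly the same figure for both patterns. In A, pre-frailty carries almost no extra odds; in B it carries nearly five-fold odds. The pooled ratio also moves with the frailty mix, enough to reverse the order of A and B. The odds ratios for impairment do not move.

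*A gentler case.* With risks of 5/15/40% at 40/30/30, the cumulative odds ratios are 7.21 and 6.51 and the pooled value is 6.66. Proportional odds nearly holds, so the pooled ratio is a fair summary of the model as written. It still equals neither odds ratio for impairment: 3.35 (pre-frail) and 12.67 (frail).

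**The case against.** **Only an association may be wanted.** The study design overview and Table 3 speak of association without direction, and a model in either direction tests whether one exists. This stands, and the model as written is not useless. It does not remove the contradiction within the Aim 4 paragraph or the mismatch with goal 4.

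**The sentence may be a slip.** The authors may have meant the VA-FI as predictor of a graded functional outcome; Table 1 records both difficulty and needing help. That would fit the word exposure, but not the inference sentence. It is possible, so the finding is that the roles conflict, not that the reversed model is certainly intended.

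**The illustration is chosen to show the problem.** This is fair. Patterns A and B break proportional odds in opposite directions. With 5,000 veterans, the scale in the power section, and no clustering, a likelihood-ratio check of proportionality would give about 33 in A and 64 in B on one degree of freedom, so a routine check would expose it. Under the 5/15/40% gradient, category risks back-calculated from the fitted model and the overall impairment rate come close to the true ones (about 5/14/40%). A reader might therefore infer that the model as written can never show how impairment varies with frailty; that is too strong. The plan does not propose back-calculation, however, and it fails when proportional odds does (for example about 10/20/39% recovered against true risks of 5/30/34%). The article says only ordinal logistic; a common odds ratio is the usual default but is not stated.

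**The stake could be overstated.** A reader might infer that Aim 4 will decide which frailty categories trigger functional screening. The article does not say so. The initiative screens all veterans aged 60 and over annually, and the stated purpose is to learn how the two approaches complement each other.

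**Conclusion.** The point holds as an internal contradiction with a practical consequence. The Aim 4 paragraph gives the VA-FI two incompatible roles, and the model and inference sentences, as most naturally read, run opposite to goal 4. An analyst cannot follow every sentence. Followed as written, the analysis tests for association but does not report the odds or probability of impairment by frailty category.

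How much is lost depends on the data. It is small for category risks if proportional odds holds and someone back-calculates them. It is large if proportional odds fails, as in the illustration (about 3.1 in both patterns, against 1.11 and 3.86 or 4.75 and 6.00). Those figures rest on an assumed frailty mix, assumed risks, binary impairment and no clustering; they show what can happen, not what is expected. The contradiction depends on none of these assumptions.

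The matter should be corrected, but its reach is limited. Aim 4 is one of four goals, is not a randomised comparison, and does not touch the primary reach or referral outcomes.

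**What to change.** In the Aim 4 analysis paragraph:

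1. Make functional status the response. Use either a binary positive screen (at least one ADL or IADL, as Table 1 defines it) in a logistic mixed model, or an ordinal mixed model if the graded difficulty and help measure is used.
2. Enter VA-FI category as the predictor.
3. Account for site clustering and, because Table 3 lists several time points for Aim 4, for repeated measurements on the same veteran where more than one is used. A site random intercept alone would not do this.
4. Report pre-frail versus non-frail and frail versus non-frail odds ratios with 95% confidence intervals, and the model-based probability of impairment in each category.
5. Reword the inference sentence so that the odds ratios are those for VA-FI category.

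If the authors want only a symmetric association, the alternative is to drop the word exposure and restate goal 4 to match; the analysis would then no longer address identification of veterans at risk.

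The cost is a few sentences, with the same data and software. The small downside is two contrasts to report instead of one odds ratio.

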**Aim 4. Effectiveness of EHR-based frailty screening**								
Association of EHR frailty indices with functional status	VA-FI, JEN FI	X		X	X	X		X

Abbreviations: *CDW* Corporate Data Warehouse, *GECDAC* GEC Data & Analysis Center, *RHF* Residential History File, *VA-FI* VA Frailty Index

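### Aim 4 sets out to test frailty screening for veterans at risk of impairment, but its model makes frailty the outcome and current function the predictor, so it shows association and not who will become impaired

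*Protocol article*

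**What the plan says.** Under Study goals and objectives, the fourth goal is to "test the effectiveness of electronic health record (EHR)-based frailty screening for identifying veterans at risk for functional impairment".

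The Overview of study design gives the motive: the operational partners' interest in "developing proactive approaches to identify high-risk veterans and intervene to prevent or delay functional impairment and associated acute care utilization". It adds a premise about time order: "Because frailty typically develops before functional impairment and may be a promising target for intervention". The test it then announces is one of association: "we will test the association of clinic-collected functional status measures with automated EHR-based frailty measures". It closes with a softer purpose, that the results will show how the two approaches can complement each other.

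The section Analysis plan, aim 4 names frailty, measured by the VA-FI in three categories, as the primary exposure. The model is an "ordinal logistic mixed modeling strategy to estimate the association of clinic-collected functional status measures on frailty", and inference rests on odds ratios for the functional status measures. Table 3 lists the Aim 4 measure as "Association of EHR frailty indices with functional status", marked at pre-implementation, Periods 1 to 3 and six months of Sustainment.

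**The concern.** Two things do not line up.

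- **Roles of the variables.** Frailty is named as the exposure but sits on the outcome side of the model. A screening question runs the other way: given the index, how likely is impairment?
- **Goal against estimand.** A goal about identifying veterans at risk, motivated by prevention, needs either the accuracy of the index against the screen or the risk of later impairment by index level. The plan reports neither.

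What is at stake is how the result is read. A clear association could be taken as support for prevention triggered by the frailty index. The same association would appear if coded health deficits merely accompany disability that is already present and that the clinic screen finds directly.

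**Working it through.** The document gives no sample size, effect size or power for Aim 4, so there is no stated figure to reproduce. The check has four steps.

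**1. Goal and analysis side by side.**

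| Element | Goal and motive | Aim 4 analysis plan |
|---|---|---|
| Predictor | EHR frailty index | Functional status measures |
| Outcome | Functional impairment | VA-FI category |
| Time order | Frailty assumed to come first | None stated |
| Population | Veterans at risk | No restriction to the unimpaired stated |
| Quantity | Effectiveness of screening | Odds ratio for functional status |

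**2. What an odds ratio leaves open about accuracy.** For one VA-FI cut-off against a positive or negative screen, OR = [sens/(1 − sens)] × [spec/(1 − spec)].

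- Sensitivity 50%, specificity 75%: (0.50/0.50) × (0.75/0.25) = 1 × 3 = 3.
- Sensitivity 75%, specificity 50%: (0.75/0.25) × (0.50/0.50) = 3 × 1 = 3.

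The odds ratio is the same for two quite different screening tools.

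**3. What it leaves open about later impairment.** A simulation of 40,000 veterans per scenario used impairment prevalence 459,000/2,800,000 = 16.4%, from the Background (ages 65 and older). All other parameters are assumed. Current impairment raised the odds of a higher frailty category about threefold. New impairment among the unimpaired followed a logistic model with intercept −2.5 and slope 0, 0.35 or 0.7 per frailty level.

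| Assumed slope | OR, frailty category on current impairment | OR per frailty level, new impairment |
|---|---|---|
| 0 | 2.97 | 1.00 |
| 0.35 | 2.94 | 1.50 |
| 0.7 | 2.99 | 1.97 |

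The planned type of estimate barely moves, whether frailty predicts new impairment strongly or not at all.

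**4. Whether a time-ordered analysis is feasible.** Screening is annual, and follow-up is 12 months of Implementation plus 6 of Sustainment. Veterans first screened in months 0–6 are due again in months 12–18. The estimate of more than 5,000 veterans comes from the power section. The remaining inputs are assumptions: all 5,000 are screened, half of first screens fall in months 0–6, 60–80% of those veterans are re-screened, and 5–10% become impaired.

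- Unimpaired at first screen: 5,000 × (1 − 0.164) = 4,180.
- Re-screened: 4,180 × 0.5 × 0.6 = 1,254, up to 4,180 × 0.5 × 0.8 = 1,672.
- Incident cases: 1,254 × 0.05 ≈ 63, up to 1,672 × 0.10 ≈ 167.

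The Hanley-McNeil standard error at AUC A = 0.70, with n1 cases and n0 non-cases, is SE² = [A(1 − A) + (n1 − 1)(q1 − A²) + (n0 − 1)(q2 − A²)]/(n1·n0). Here q1 = A/(2 − A) = 0.538 and q2 = 2A²/(1 + A) = 0.576.

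- 63 cases among 1,254: SE = 0.038.
- 167 cases among 1,672: SE = 0.023.
- A less favourable case, 30 among 600: SE = 0.055.

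These ignore clustering. If the Aim 3 design effect of 4.4 applied, which is itself an assumption, each is multiplied by √4.4 = 2.10. The first two become about 0.079 and 0.049.

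**The case against.** The strongest reply is that the plan promises no more than it delivers. The design overview announces a test of association and a look at how the two approaches complement each other, and the analysis plan and Table 3 provide that. The Description of intervention uses the at-risk phrase to explain the age-60 cut-off, which fits a triage reading: whom to screen now. A concurrent association can inform that. The odds ratio for a two-by-two table is also the same in either direction, so the swapped roles do not by themselves spoil evidence of association. Finally, this is a condensed article, and lags and cohort restrictions may be set out in an analysis plan that is not shown.

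Much of this stands. A reader might infer that the document commits to a cross-sectional analysis of all screened veterans. It never says so. That is inferred from the absence of any lag or unimpaired cohort, and Table 3 does list repeated time points. A reader might also infer that goal 4 itself speaks of veterans before impairment develops. That sense comes from the design overview's motive and premise, not from the goal's wording.

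What does not fall away is what the text fixes: the outcome, the predictor and the inferential quantity. The exposure is contradicted within one section. Even on the triage reading, effectiveness of screening calls for accuracy measures, which odds ratios for functional status do not supply.

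The objection also limits the remedy. Screening frequency is named as a possible site adaptation. Re-screens would fall in Sustainment, after implementation support is withdrawn. The run-in is not a marked Aim 4 time point in Table 3, although screening data from it are used to identify sites with low Reach.

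**Conclusion.** The concern holds in this form: the Aim 4 analysis reverses its own named exposure and yields an odds ratio that speaks to association with measured function. It does not give the accuracy of the frailty index as a screen, nor show which veterans will become impaired. The point is worth correcting, but it concerns one of four goals and touches neither the primary implementation outcome nor the primary effectiveness outcome.

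The contradiction over exposure and outcome rests on the text alone. The limit on prediction rests on no lag, unimpaired cohort or incident outcome being stated; the simulation illustrates it under assumed parameters. The 63–167 cases and standard errors of 0.023–0.038 are illustrative only. They use a prevalence for ages 65 and older in a trial enrolling from 60, assumed re-screening and incidence rates, and no allowance for clustering.

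It would go too far to say that the planned association is worthless or should give way to a prospective analysis. It answers the softer purpose in the design overview and should be kept.

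**What to change.** 1. Make functional impairment the outcome and VA-FI, measured before the screen, the predictor. Report discrimination, for example AUC plus sensitivity and specificity at the VA-FI category cut-offs (0.1 and 0.2), with site clustering accounted for.
2. Add an analysis among veterans who screen negative at their first screen, relating earlier VA-FI to a positive result at the next screen available by the end of Sustainment.
3. Keep the planned association, labelled as agreement with current impairment. If too few veterans are re-screened, limit the Aim 4 conclusion to that and word the goal to match.

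**Cost.** No new visits are needed; the work is added analysis of screening and frailty records. Run-in screens would have to be listed as an Aim 4 data source if the added cohort uses them. Only re-screened veterans contribute to item 2. Their return may be selective and must be described, and precision cannot be promised because the document gives neither a re-screening rate nor an incidence rate.

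### Aim 4 names frailty as the exposure but models it as the response, and the planned odds ratio alone does not measure how well frailty screening identifies impairment

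*Protocol article*

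**What the plan says.** All references are to the protocol article.

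- **Study goals and objectives.** The fourth goal is to "test the effectiveness of electronic health record (EHR)-based frailty screening for identifying veterans at risk for functional impairment". Frailty is the screening measure and impairment is what it should find.
- **Analysis plan, aim 4 (Frailty), exposure.** "Our primary exposure for Aim 4 is ‘frailty’ operationalized using the VA-FI".
- **Same section, form of the variable.** "We will model the VA-FI as a 3-level categorical measure (i.e., non-frail, pre-frail, frail").
- **Same section, model.** An ordinal logistic mixed model is planned "to estimate the association of clinic-collected functional status measures on frailty".
- **Same section, inference.** "Inference will be based on estimated odds ratios associated with functional status measures".
- **Aim 4 (Frailty), under the outcome measures.** The VA-FI has cut-points at 0.1 and 0.2, which separate non-frail, pre-frail and frail. Functional status comes from Health Factors data.
- **Overview of study design, and the Aim 4 row of Table 3.** Both describe the measure as an association between functional status and the frailty indices, without direction. The overview adds that frailty usually comes before impairment.

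**The concern.** One variable cannot be both the exposure and the modelled response. Three features of the section make the VA-FI the response: only the VA-FI is given ordered levels to suit the ordinal link, functional status is said to act on frailty, and the reported odds ratios belong to functional status. Only the opening sentence makes it the exposure.

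Goal 4 asks how well a frailty score picks out veterans at risk of impairment. A reader who wants to use the score needs two things: the risk of impairment in each frailty category, and the accuracy of flagging at a cut-point. The result the section plans to report is a cumulative odds ratio for being in a higher frailty category, comparing veterans by functional status. It gives neither directly. An analyst would also have to guess which direction was meant.

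**Working it through.** The article states no sample size, power or effect size for Aim 4, so there is no figure of its own to reproduce.

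**1. Do the two directions give the same information?** The data below are assumed: 6,000 veterans, binary impairment, no clustering. The planned direction is a proportional-odds model of frailty category on impairment. The direction Goal 4 implies is a logistic model of impairment on frailty category.

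| Case | Non-frail / pre-frail / frail | Impairment risk in each | Planned: one cumulative OR | Goal 4: pre-frail OR, frail OR (vs non-frail) |
|---|---|---|---|---|
| a | 40 / 30 / 30% | 8 / 15 / 30% | 3.43 | 2.03, 4.93 |
| b | 20 / 30 / 50% | 8 / 15 / 30% | 3.16 | 2.03, 4.93 |
| c | 40 / 30 / 30% | 5 / 20 / 25% | 3.22 | 4.75, 6.33 |

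From (a) to (b) the risks of impairment are unchanged, yet the planned odds ratio moves from 3.43 to 3.16. From (a) to (c) the risks differ clearly, yet the planned odds ratio is similar (3.43 and 3.22). The single odds ratio therefore does not tell the reader the risk of impairment by frailty category.

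**2. Can the planned model still speak to identification?** Yes. With frailty as the response, P(VA-FI > 0.2 given impaired) is sensitivity, and P(VA-FI > 0.2 given unimpaired) is 1 − specificity. The counts in case (a) are:

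- Impaired: 192 + 270 + 540 = 1,002.
- Unimpaired: 2,208 + 1,530 + 1,260 = 4,998.
- Sensitivity at > 0.2: 540/1,002 = 0.539. The fitted proportional-odds model gives 0.537.
- False-positive rate at > 0.2: 1,260/4,998 = 0.252. The fitted model gives 0.253.
- Sensitivity at > 0.1: 810/1,002 = 0.808. The fitted model gives 0.812.

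The information is in the model, but the section bases inference on the odds ratios only. PPV also needs the prevalence of impairment, which the same data supply. In case (c) the odds ratios at the two cut-points are 5.52 (> 0.1) and 2.58 (> 0.2), so proportional odds fails and one number summarises them poorly.

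**3. Why an odds ratio alone is not enough (illustration).** Inputs:

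- Impaired: 459,000 / 2,800,000 = 16.4%, from the Background. That figure is for veterans aged 65 and over, while the trial screens from age 60, so using it here is an assumption.
- Frail among the unimpaired: 22%, range 15–30%. Assumed.
- Odds ratio: 3. Assumed.

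Odds of frail among the impaired = 3 × 0.22/0.78 = 0.846.

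Sensitivity = 0.846/1.846 = 0.458.

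PPV = 0.164 × 0.458 / (0.164 × 0.458 + 0.836 × 0.22) = 0.0752/0.2591 = 0.29.

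At 15% frail, sensitivity is 35% and PPV 31%. At 30% frail, sensitivity is 56% and PPV 27%.

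**4. Does direction change those figures?** No. Turning the same table round, the odds of impairment are 0.0752/0.1839 = 0.409 in the frail and (0.164 × 0.542)/(0.836 × 0.78) = 0.136 in the non-frail. The ratio is again 3.0. For a binary contrast the unadjusted odds ratio is symmetric.

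**The case against.** The strongest defence is that Aim 4 is a plain association aim. The design overview and Table 3 word it without direction, and the overview wants to learn how the two approaches complement each other. An odds ratio serves that purpose, and a test of no association would usually reach the same conclusion either way. In case (a) the odds ratios at the two cut-points are 3.34 and 3.47, so one cumulative odds ratio describes them well. AUC, look-back dates for the codes and the form of the confidence intervals are details an article may leave to an analysis plan.

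Most of this stands and limits the weight of the point. It does not remove the contradiction, because the article itself states the exposure, the model and the estimand, and they do not agree. The neutral wording elsewhere does not say which is meant, and the goal and the Aim 4 title in Table 3 both speak of the effectiveness of frailty screening.

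Two stronger readings are tempting and are not supported. A reader might infer that the planned model cannot answer Goal 4. Step 2 shows that sensitivity and specificity can be derived from it. A reader might also take the 46% and 29% as the damage done by the reversal. Step 4 shows they are the same in either direction, and they rest on assumed inputs.

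**Conclusion.** The point holds in limited form. The Aim 4 analysis section declares the VA-FI the exposure and specifies a model in which it is the response. The planned odds ratio does not directly give the risk of impairment by frailty category and is not on its own a measure of identification, which is what Goal 4 is about.

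The contradiction rests on the text alone. The size of any practical consequence cannot be read from the documents. The worked cases show only that the directions are not interchangeable for a 3-level index and that an odds ratio of 3 is compatible with modest accuracy.

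This should be fixed, but it is not critical: Aim 4 is outside the randomised comparison, and neither primary outcome named in the abstract depends on it.

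**What to change.** Rewrite the Aim 4 analysis section so that functional impairment is the outcome of a mixed logistic model with a site random effect and VA-FI category is the predictor. This agrees with the sentence that names frailty as the exposure. Alongside the odds ratios, report sensitivity, specificity and PPV at the existing VA-FI cut-points (> 0.1 and > 0.2).

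If the authors want only a non-directional association, the least they should do is drop the word exposure, state which variable is the response, and bring the wording of Goal 4 into line.

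The cost is analysis wording. The data already planned are sufficient, and nothing changes in conduct or sample size.
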